#### Randomisation

Consenting participants will be randomised to CBT manual plus therapist support or Fatigue Information Sheet only using a random number generator with a 1:1 ratio in the Statistical Package for the Social Sciences Version 22. All baseline information will be collected prior to randomisation. Participants will be randomised at the individual level. The randomisation sequence will be generated electronically by an independent statistician prior to the commencement of the study. The statistician will have no patient contact. The trial coordinator (blinded until this point) will access the randomisation database to assign patients to the two groups. Indeed, as this is a small pilot study on a limited budget, there are no resources available to provide a blinded data collector. Owning to the nature of the study the participants, the researchers and the therapist will not be blinded to treatment allocation after randomisation. The trial coordinator will be informed of the outcome of the randomisation procedure in order to identify participants who require telephone support calls during the trial. The researcher conducting the qualitative interviews will also be unblinded to ensure that appropriate questions are asked.

#### Group 1 (CBT manual + therapist support)

Group 1 participants will receive a CBT manual for the management of fatigue and have one 60-min session and seven 30-min telephone/Skype sessions with a therapist over an eight-week period. All sessions will be over the telephone or Skype according to patient preference. In the Consent Form, patients will be informed that if they choose Skype, information may not be secure and may be transferred to other countries outside the Trust’s control. During the intervention, participants will have access to all usual care, including the nurse-led helpline.

#### CBT manual development

The CBT manual utilised for the intervention will be a modification of the CBT manual for the management of MS fatigue developed by Van Kessel et al. [57]. The manual contains eight sessions. Despite, the lack of consensus from systematic reviews on the adequate number of therapy sessions to be used by interventions, the number of sessions was modelled on the number of sessions utilised in the RCT by Van Kessel et al. [57], where 100% of the subjections in the CBT group completed the eight-session intervention with large effect sizes. The sessions include: IBD fatigue explained; CBT for IBD fatigue; activity scheduling; improving your sleep; understanding IBD symptoms; changing your thinking; managing stress, determining a sense of control and coping with emotions; social support and preparing for the future, and it has an approximate length of 100 pages. One of the authors ([name]) of the original CBT manual for MS helped in making the initial changes and refinements to the manual incorporating evidence from the first MS trial [57] and its adaptation into an Internet-based CBT self-management programme for fatigue in MS [104].

In order to make the intervention relevant and acceptable to patients with IBD, we have worked with people with IBD-fatigue, consultant gastroenterologists, IBD-nurse specialists, dieticians and psychologists working with people with IBD. Specifically, Session 1 of the intervention manual ‘IBD-Fatigue Explained’ addresses medical factors causing fatigue which are specific to patients with IBD including inflammation and fatigue and anaemia and fatigue. Furthermore, examples and tasks throughout the intervention manual have been adapted to reflect concerns and issues specific to patients with IBD and not MS. Finally, a medical writer conducted in-depth pre-post readability statistics and performed the required changes to transform the intervention manual into plain English and make the language as clear as possible. Likewise, a graphic designer made the necessary formatting edits to the manual so as to make the design more user-friendly.

#### Therapists

Patients will have telephone support sessions with one of two qualified CBT therapists who have experience in delivering interventions to patients with long-term conditions. The therapist will receive the manual in advance and have the opportunity to discuss its contents and any questions with the research team. The purpose of the telephone/Skype support calls are to promote engagement with the intervention and to support the patient in collaboratively developing goals to work on using the resources and information available to them in the CBT manual. At the start of each telephone call, the therapist will set an agenda with the participant. The first telephone/Skype support call will be scheduled for when the participant will have completed the first session in the CBT manual.

#### Feasibility and acceptability outcomes

Feasibility of recruiting eligible patients will be evaluated by calculating the proportion of those invited to take part in the intervention that were eligible and then were consented into the trial. The willingness of participants to be randomised will be evaluated by calculating the proportion of those who dropped out of the trial after they have been randomised. Refusal, withdrawal and dropout rates from the study and number of sessions with therapist will be recorded. A post-intervention follow-up questionnaire included in *Outcome Data B* booklet will assess compliance rates to the intervention by asking participants about the number of sessions of the manual they read and time per week spent completing tasks in relation to the intervention. The therapist/s will also record how many sessions the participants have completed. Furthermore, in order to assess compliance to the intervention procedures, if participants are willing to do so, they will be asked to provide the research team with the Homework Sheets completed at the end of each session in the manual. The Homework Sheets will be checked for completion in order to assess compliance with the intervention components.

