## Methods and design

This study will assess the feasibility and initial estimates of efficacy of a CBT intervention for the management of fatigue in patients with IBD. The pilot intervention will have the objectives to:Assess the feasibility of recruiting eligible patients;Assess the willingness of participants to be randomised;Evaluate the compliance rates to the intervention (Therapist Sessions and Homework Sheets);Assess withdrawal and dropout rates during the treatment phase;Assess the completion rates of the outcome measures post intervention and at follow-up times;Determine the adequate sample size for definitive full-scale effectiveness RCT;Obtain initial estimates of efficacy on fatigue and QoL in the CBT intervention group compared to the fatigue Information Sheet group;Obtain detailed qualitative feedback from patients, the therapist/s delivering the intervention and HCPs working with patients with IBD on their experience and views of the intervention and areas for improvement in future fatigue interventions.

The pilot trial will not attempt to provide evidence of clinical effectiveness for the CBT intervention in people with IBD. This is in accordance with the recommendations from the National Institute of Healthcare Research (NIHR) guidelines and the Consolidated Standards of Reporting Trials (CONSORT) for the development of pilot studies [91, 103].

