Eligible patients will then be given at least 48 h to consider their participation in the study and discuss the decision with family, friends and their care team. A member of the research team will then contact them by telephone to answer any additional questions, verify their understanding of what is involved and confirm their interest in study participation. If patients agree to take part in the study, they will be asked to sign the *Patient Consent Forms-RCT* and complete the *Baseline Data A* booklet. A format for written questions for this phase has been developed and piloted with our PPI group to ensure acceptability and ease of understanding of questions to be asked. Participants will be asked to return the signed *Patient Consent Forms-RCT* and the completed questionnaires in the pre-paid stamped addressed envelope provided within seven days of receipt. The returned study documents will be checked for completeness, and the patient will then be entered into the randomisation database for the RCT and told whether they are in Group 1 (CBT manual + therapist support) or Group 2 (Fatigue Information Sheet only). Screening and consenting will continue until the study target sample size (*n* = 40, 20 for each arm) is reached. Hospital consultants will be informed of the patients’ participation in the study via an entry made in the patient’s notes; with patients’ agreement, their General Practitioner (GP) will be informed using *GP Notification Letter*.

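### Willingness to be randomised is measured by dropout after randomisation, a ratio that does not respond to how many informed patients decline

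*Protocol article*

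**What the plan says.** The objectives under Methods and design include "Assess the willingness of participants to be randomised" and, as a different item, "Assess withdrawal and dropout rates during the treatment phase".

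Under Feasibility and acceptability outcomes, the first of these is given its measure: "willingness of participants to be randomised will be evaluated by calculating the proportion of those who dropped out of the trial", with dropout counted from randomisation onwards. The sentence before it gives the recruitment objective a different measure: "calculating the proportion of those invited to take part in the intervention that were eligible and then were consented into the trial". The sentence after it says that refusal, withdrawal and dropout rates will be recorded, without tying refusals to a particular objective.

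Recruitment and Randomisation fix the order of events. A patient hears about the trial from a researcher in clinic. Those who show interest are screened for eligibility. Eligible patients have at least 48 hours to decide, followed by a telephone call to "answer any additional questions, verify their understanding of what is involved and confirm their interest in study participation". Signed consent and the baseline booklet come back by post. Only after that does the article say that "the patient will then be entered into the randomisation database for the RCT and told whether they are in Group 1" or Group 2. The Randomisation section agrees: "Consenting participants will be randomised to CBT manual plus therapist support or Fatigue Information Sheet only".

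**The concern.** Willingness to be randomised is settled before randomisation, when an informed patient agrees or declines to let chance decide the arm. The stated measure is taken only among people who agreed. Someone who declines because they do not want to be randomised is outside both numerator and denominator. Someone who leaves later through illness or lack of time counts as if unwilling to be randomised.

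The comparison is a manual with eight therapist sessions against an information sheet, so a preference for one arm is a plausible barrier to recruiting the definitive trial. A low dropout figure could be reported as good willingness to be randomised even if many of those approached had declined for exactly that reason. Reasons for refusal are hard to recover afterwards, so the definition is best settled before recruitment starts.

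**Working it through.** The article gives no figure for willingness to be randomised, so there is none to reproduce. The check is how the stated measure behaves.

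**Inputs** (Statistics and data analysis): target 40 randomised, 20 per arm; about 40% of eligible patients recruited; about 20% attrition at each follow-up. Treating attrition as dropout is my assumption (see the objection).

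**Step 1: who enters the measure.** Measure = dropouts after randomisation / randomised. All those randomised have consented, so decliners contribute to neither part.

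**Step 2: size at the plan's uptake.** Eligible patients needed = 40 / 0.40 = 100. Decliners = 100 − 40 = 60, none of whom enters the measure. Dropouts at 20% = 0.20 × 40 = 8, so the measure is 8/40 = 20%, exact (Clopper-Pearson) 95% CI 9.1% to 35.6%.

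**Step 3: response to refusals.** The 40% row is the plan's figure; the other uptakes are an assumed range.

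| Uptake among eligible | Eligible | Decline | Consented / eligible (exact 95% CI) | Stated measure |
|---|---|---|---|---|
| 10% | 400 | 360 | 10% (7.2% to 13.4%) | 8/40 = 20% |
| 20% | 200 | 160 | 20% (14.7% to 26.2%) | 8/40 = 20% |
| 40% | 100 | 60 | 40% (30.3% to 50.3%) | 8/40 = 20% |
| 80% | 50 | 10 | 80% (66.3% to 90.0%) | 8/40 = 20% |

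The last column stays the same while the number declining runs from 10 to 360.

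**Step 4: response to other things.** No time point is set for the measure. If 20% are lost at each follow-up and the losses compound, 40 × 0.8 = 32 remain at three months, 32 × 0.8 = 25.6 at six and 25.6 × 0.8 = 20.5 at 12. Cumulative loss is then 20% at three months and 1 − 0.8³ = 48.8% at 12. The measure could lie anywhere in that span with no change in willingness to be randomised.

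**The case against.** The strongest reply is that the trial already collects most of what is needed. The consent proportion follows an explanation of the RCT, so it is in effect consent to be randomised, and refusals are recorded. This stands. A reader might infer that the objective cannot be answered at all, or that the definitive trial would be planned with no estimate of acceptance. The documents do not support that: decliners are missing from the measure assigned to this objective, not from the trial. What remains is that the article gives the consent proportion to recruitment, starts it from those invited (so ineligibility and refusal are mixed), and does not link refusals to willingness.

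A second reply is that dropout carries some signal. Allocation is open, and leaving on learning of the information-sheet arm partly reflects reluctance to be randomised. This also stands, but the stated ratio does not separate such departures by timing, reason or arm. The interviews cover randomisation too, though only among about seven people who had consented.

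Third, the illustration should not be over-read. A reader might conclude that 8 of 40 patients will be reported as unwilling. The article does not say that an unreturned booklet counts as leaving the trial, and it distinguishes withdrawal from the intervention from complete withdrawal. Nor are the two objectives shown to yield one identical number: the dropout objective is limited to the treatment phase, and the willingness measure has no such limit.

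Finally, a reason-for-refusal field may exist in the full protocol or its forms. Its absence from a journal article is not a finding. The finding is the definition that the article does state.

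**Conclusion.** The point holds as a wrong stated definition: an objective about accepting randomisation is measured only in those who have accepted it. The measure reflects retention or acceptance of the allocated arm, overlaps with the dropout objective, and does not change with the number of informed patients who decline. That conclusion rests on the order of events in the article and needs no numerical assumption.

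The size is illustrative. At the plan's 40% uptake, about 60 of 100 eligible patients fall outside the measure. The 20% reading (exact 95% CI 9.1% to 35.6%) depends on equating dropout with the assumed attrition.

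This should be fixed, but it does not undermine the pilot. It concerns one descriptive objective of eight, the article ties no progression rule to it, and the main counts are already collected.

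**What to change.** Replace the sentence under Feasibility and acceptability outcomes with a definition built on consent:

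- **Willingness to be randomised:** the proportion who consent to randomisation among patients given the full explanation of the RCT and, separately, among those confirmed eligible, each with a 95% CI. Both denominators are needed because the explanation comes before eligibility screening, so people put off by randomisation at that stage never have their eligibility confirmed. Show patients screened as ineligible as a separate count, so that they are not read as refusals.
- **Reasons:** the share of refusals attributed to randomisation or to preference for an arm, from an optional, anonymous main reason. Note it both at the clinic explanation and at the call after 48 hours; the call alone would miss those who decline in clinic. Report unknown reasons as unknown.
- **Dropout:** report post-randomisation dropout, by arm, under the withdrawal and dropout objective only.

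The cost is one sentence in the protocol and one screening-log field, with no extra patients. The new ratio partly overlaps with the recruitment proportion, so the reasons for refusal are what give this objective content of its own. Because they are optional, they will be incomplete.

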#### Initial estimates of efficacy outcomes

Prior to randomisation, eligible participants will complete the study baseline measures which are contained in a single questionnaire booklet. The questionnaire booklet contains 20 printed pages. Preliminary piloting has demonstrated that on average it has taken 10–15 min to complete and our patient representatives have commented that this is not unduly burdensome. Three months post randomisation, the Outcome Questionnaire booklets will be sent by post. Patients who were allocated to the CBT intervention and will be asked further questions about their experience of completing the intervention in order to assess their compliance with the intervention, preferences, acceptability and satisfaction with the intervention. Patients who were allocated to Fatigue Information Sheet only, will be asked about their experience of reading the Fatigue Information Sheet. A postal reminder will be sent to non-responders two and four weeks after the seven-day response period has ended, utilising the Reminder Letter and/or a telephone call*.* Six and 12 months post randomisation, two more outcome booklets will be sent respectively, with two postal reminders and/or telephone calls for non-responders after two and four weeks. The booklets will only contain the primary outcome measures IBD-fatigue, QoL UK questionnaire and Disease Activity Indexes (DAIs) specific to the condition.

#### Twelve months post randomisation

Patients in the Fatigue Information Sheet only group (Group 2) will be offered the CBT manual for managing fatigue in IBD. No therapist support will be offered alongside the manual.

Nested qualitative study (*n* = 7 patients + both therapist/s + approximately three HCPs)

To better understand patient perspectives on the intervention, participants consenting to the RCT might be invited for interview. The interview sub-sample will be purposively selected to include both genders, a range of ages, both IBD diagnoses and those successful and not successful in showing an initial improvement in IBD-fatigue. Purposive sampling has the potential to provide richer, more relevant and diverse data pertinent to the research question [105, 106]. Participants will be asked about the process of recruitment and randomisation, their experience of the intervention itself, their reasons for dropping out or not completing (where appropriate) and areas for improvement in the design of future fatigue interventions for patients with IBD. Patients will receive information about the interviews in the *Patient Information Sheet – RCT and Interviews*. Using the *Patient Consent Form – Interviews*, separate informed consent will be sought for the face-to-face/telephone/Skype, semi-structured interviews with a purposive sample of approximately seven participants (about one-third of the participants in Group 1). Interviews will be conducted by a researcher not involved in the delivery of the intervention and have a duration of 30–60 min.

The nested qualitative study will be conducted after the three-month follow-up quantitative data collection point. The choice of qualitative data collection at three months allows for minimisation of recall bias, patient burden and confounding of participants in the study. The short time period between the intervention and the interviews, ensures that participants will find it easier to recall their experience of the intervention. Indeed, involvement in qualitative data collection as part of an RCT may in some way influence the participant’s experience of treatment [107]. However, the gap in time between the interviews and the next follow-up data collection point (six months post randomisation) limits the potential for participants’ outcome responses to be influenced by their participation in the interviews. Furthermore, time gap in time between interviews and follow-up questionnaire completion reduces potential patient burden, while still ensuring continuity to the study.

The therapists supporting patients during the intervention will be interviewed to understand their experience of delivering the intervention and to inform future adaptation and delivery of the intervention in clinical practice. HCPs working with patients with patients with IBD at the study site will be interviewed to obtain their views on the intervention and its possible implementation within existing IBD service at a roll out stage. Approximately three HCPs will be interviewed. Informed consent for the interview will be secured using the *Staff Consent Form – Interviews.*

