Primary and secondary measures at baseline along with recruitment rates, telephone session attendance, time spent on the intervention, Homework Sheet completion rates and withdrawal from intervention rates will be presented as means and standard deviations for approximately normally distributed continuous variables, medians and interquartile ranges for non-normally distributed variables, frequencies and percentages for categorical variables. Initial estimates of treatment effect on primary and secondary outcomes at the follow-up assessments will use an intention-to-treat (ITT) framework, implemented using a regression model, adjusting for baseline values of the outcome, sociodemographic and clinical outcomes. ITT analysis will compare the primary and secondary outcome measures at three months between the two randomised groups. ITT analysis will compare only primary outcome measures at six and 12 months between the two randomised groups. Where participants wish to withdraw from the intervention, we will attempt to retain them in the data collection, unless they express a wish to be withdrawn completely.

As this is a pilot study, it is not intended that the study is powered to detect significant differences on the primary or secondary outcome measures. Qualitative data will also be recorded. Protocol conforms to Standard Protocol Items: Recommendations for Interventional Trials (SPIRIT). See Additional files 1 and 2 at the end of the manuscript for SPIRIT Figure and Checklist.

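### Group 2 is offered the CBT manual at 12 months, when its last booklet is posted and before reminders end, so late control answers may follow exposure to the manual

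*Protocol article*

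**What the plan says.** Four statements in the protocol article bear on the point.

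- **Offer to controls.** Under the heading "Twelve months post randomisation" the article says: "Patients in the Fatigue Information Sheet only group (Group 2) will be offered the CBT manual for managing fatigue in IBD". It adds: "No therapist support will be offered alongside the manual". No condition about the outcome booklet is attached.
- **Last outcome booklet.** The section on initial estimates of efficacy outcomes says: "Six and 12 months post randomisation, two more outcome booklets will be sent respectively". The same sentence continues "with two postal reminders and/or telephone calls for non-responders after two and four weeks". It does not say when the reminder clock starts.
- **Reminder clock at three months.** For the earlier booklet the same section is more explicit: "A postal reminder will be sent to non-responders two and four weeks after the seven-day response period has ended".
- **Use of the data.** Statistics and data analysis says: "ITT analysis will compare only primary outcome measures at six and 12 months between the two randomised groups".

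The primary outcome is a self-completed fatigue scale, and the Randomisation section states that participants know their allocation.

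**The concern.** The offer and the last booklet share one nominal time, and the booklet then stays open for some weeks. If staff follow the stated timing, a control who replies after a reminder may by then hold the intervention manual. If the manual helps, that answer looks better than it would have under the control condition, and the 12-month difference shrinks. The offer alone might also alter how an unblinded participant rates fatigue.

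The 12-month contrast matters to this trial. The Background criticises previous psychosocial interventions because their effects faded, and asks for at least 12 months of follow-up to see whether benefit lasts. The pilot also has few controls, so a handful of late answers carries weight. The people affected are those whom the reminders are meant to recover.

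**Working it through.** The plan gives no figure for this overlap, so there is none to reproduce. The check covers timing, then the weight of one answer, then an illustration of size.

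**1. Length of the overlap**

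- Manual offer: 12 months (day 0).
- Booklet posted: 12 months (day 0).
- Last reminder, 12-month sentence read literally: 4 × 7 = 28 days.
- Last reminder, if the three-month response period carries over: 7 + 28 = 35 days.

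The overlap to the last reminder is 28 to 35 days. Answers prompted by that reminder come later still. No section puts booklet return before the offer.

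**2. Weight of one control answer**

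Statistics and data analysis plans 20 per arm and expects about 20% attrition for each follow-up.

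- Loss occurring once: 20 × 0.8 = 16 controls, so one answer is 1/16 = 6.25% of the control data.
- Loss compounding over three follow-ups: 20 × 0.8³ = 10.24, about 10 controls, so one answer is about 10%.

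**3. Illustrative dilution (assumed inputs, not from the document)**

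Dilution of the 12-month difference = f × g. Here f is the share of control answers given after exposure, and g is the share of the treatment effect gained from the manual by then.

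| f | g = 0.10 | g = 0.25 | g = 0.50 |
|---|---|---|---|
| 0.10 | 1.0% | 2.5% | 5.0% |
| 0.25 | 2.5% | 6.2% | 12.5% |
| 0.40 | 4.0% | 10.0% | 20.0% |

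If a later trial were sized on the diluted effect, its size would be multiplied by 1/(1 − dilution)². That is 1/0.99² = 1.02 at the low end and 1/0.80² = 1.56 at the high end.

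**4. Set against sampling error**

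With 16 per arm, the unadjusted standard error of a standardised difference is about √(2/16) = 0.35 SD. The 95% interval is then roughly ±1.96 × 0.35 = ±0.7 SD.

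**5. After the change**

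If the offer follows booklet receipt or the close of the reminder window, f = 0 for answers given within the window, and dilution from this source is 0%. The sample size does not change.

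**The case against.** The strongest reply has four parts.

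**The sections do not contradict each other.** The twelve-month section is a brief end-of-study courtesy under a nominal time heading. It does not say that the manual goes out with the booklet or before its return. This stands: the two sections overlap in time but are compatible, and a reader who inferred a contradiction would go too far.

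**The order of mailing is operational detail that an article may omit.** This stands only in part. The article states both times, and they coincide. A later analysis plan cannot undo exposure that came before the answer. The authors also thought about this kind of influence: the nested qualitative section explains that interviews were spaced away from the next questionnaire so that they would not affect outcome responses. The 12-month control answers have no such stated protection.

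**An offer is not exposure.** A control must accept the manual, receive it and work through about 100 pages without a therapist. Group 1 covers the same material over eight weeks with one. A few weeks of unguided use is likely to do less. This stands, and is why the effect is probably modest.

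**The trial is a pilot with wide intervals.** It disclaims evidence of effectiveness, and any plausible shift lies well inside ±0.7 SD. This stands as a limit on the consequences. It is no reason to leave in a bias that one sentence removes.

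A reader might also infer a large distortion. If half of control answers were late and each gained 0.3 SD, the loss would be 0.50 × 0.3 = 0.15 SD. Against an assumed effect of 0.4 SD that is 38%, and a trial sized on the remainder would be (0.4/0.25)² = 2.6 times too large. The documents support none of these inputs, and 0.3 SD would be three quarters of the assumed effect, gained from an unguided manual within weeks. Nor do they say that the definitive trial will be sized on the observed 12-month effect.

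**Conclusion.** The point holds as a matter of sequencing. As written, the offer to Group 2 and the last booklet fall at the same nominal time, and non-responders are pursued for 28 days (35 if the three-month response period applies). A late control answer in an unblinded, self-reported outcome may therefore follow the offer or use of the manual.

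If the manual helps, the bias pulls the 12-month contrast towards no difference. Its size cannot be computed from the document. The 1% to 20% range rests wholly on assumed shares of late answers and of effect gained, and a modest effect is the more likely.

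The contrast at risk is the only one at 12 months. It would be wrong to call it the only evidence on durability: the six-month contrast also bears on that and, like the three-month contrast, is unaffected.

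**What to change.** Add one sentence to the twelve-month section: the manual is offered to each Group 2 participant only after that participant's 12-month booklet has been received, or after the reminder window has closed. State when the 12-month reminder clock starts and when the window closes, since the present sentence leaves this open.

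Log two dates per control: booklet completion and manual offer. Keep any control booklet completed after the offer in the intention-to-treat analysis, and report a sensitivity analysis that excludes it. Treating such booklets as crossover data in the main analysis would depart from the stated intention-to-treat framework. Late responders may also differ from early ones, so exclusion is a check and not a correction.

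The cost is one sentence and two log entries. Some controls would wait up to about four to five weeks longer for the manual.
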